# Lateral versus conventional fasciotomy for prevention of lateral femoral cutaneous nerve injury in total hip arthroplasty with direct anterior approach: a study protocol for a dual-center, double-blind, randomized controlled trial

**DOI:** 10.1186/s13063-022-06496-2

**Published:** 2022-07-15

**Keywords:** Total hip arthroplasty, Direct anterior approach, Lateral femoral cutaneous nerve, Ultrasonography

## Abstract

**Background:**

An incision for total hip arthroplasty (THA) via the direct anterior approach (DAA) is generally made outside of the space between the sartorius and tensor fasciae latae muscles to prevent lateral femoral cutaneous nerve (LFCN) injury. Anatomical studies have revealed that the LFCN courses between the sartorius and tensor fasciae latae muscles. When the LFCN branches radially while distributing in the transverse direction from the sartorius muscle to the tensor fasciae latae muscle, it is called the fan type. Studies suggest that damage to the fan type LFCN is unavoidable during conventional fasciotomy.

We previously demonstrated that injury to non-fan variation LFCN occurred in 28.6% of patients who underwent THA by fasciotomy performed 2 cm away from the intermuscular space. This suggests that the conventional approach also poses a risk of LFCN injury to non-fan variation LFCN. LFCN injury is rarely reported in the anterolateral approach, which involves incision of fascia further away than the DAA. The purpose of this study is to investigate how the position of fasciotomy in DAA affects the risk of LFCN injury.

**Methods:**

We will conduct a prospective, randomized, controlled study. All patients will be divided into a fan variation and a non-fan variation group using ultrasonography before surgery. Patients with non-fan variation LFCN will receive conventional fasciotomy and lateral fasciotomy in the order specified in the allocation table created in advance by our clinical trial center. The primary endpoint will be the presence of LFCN injury during an outpatient visit using a patient-based questionnaire. The secondary endpoints will be assessed based on patient-reported outcomes at 3 months after surgery in an outpatient setting using the Western Ontario and McMaster Universities Osteoarthritis Index, the Japanese Orthopaedic Association Hip-disease Evaluation Questionnaire, and the Forgotten-Joint Score-12.

**Discussion:**

We hypothesize that the incidence of LFCN injury due to DAA-THA is reduced by making the incision further away from where it is typically made in conventional fasciotomy.

If our hypothesis is confirmed, it will reduce the disadvantages of DAA and improve patient satisfaction.

**Trial registration:**

UMIN Clinical Trials Registry, UMIN000035945. Registered on 20 February, 2019.

## Background

Total hip arthroplasty (THA) is an effective surgical procedure that helps reduce pain and improve function of patients with hip disorders [1, 2]. There are several surgical approaches for THA; in particular, direct anterior approach (DAA), an intermuscular and internervous approach, causes less harm to the soft tissue compared with other approaches. Thus, DAA is associated with a lower risk of dislocation and rapid recovery of muscular strength after the procedure [3, 4]. However, it may result in injury to the lateral femoral cutaneous nerve (LFCN) [5–9]. The LFCN is a pure sensory nerve that controls the anterolateral aspect of the thighs, and LFCN injury leads to hypesthesia and dysesthesia. Several studies demonstrated that LFCN injury does not affect hip joint function following THA [6, 10, 11]; however, even in such cases, sensory disturbance caused by LFCN injury may affect patient satisfaction.

The LFCN passes posterolaterally from the iliopsoas and under the inguinal ligament before it crosses between the sartorius and tensor fasciae latae muscles [12, 13]. Thus, in order to prevent LFCN injury, an incision for DAA is generally made outside of the space between the sartorius and tensor fasciae latae muscles. However, LFCN injury has been reported in 0.1 to 81% of patients [1, 6, 12, 14]. In addition to the LFCN that passes in between these muscles, Rudin et al. performed pathological examinations and identified a different type of the LFCN that radially distributes in the transverse direction from the sartorius muscle into the tensor fasciae latae muscles [15]. This variation of the LFCN, which passes across the muscles, is called the fan type, and studies suggest that damage to the fan type LFCN is unavoidable by conventional fasciotomy [15]. Moreover, we previously demonstrated that injury to non-fan type LFCN (LFCN that passes in between the sartorius and tensor fasciae latae muscles) occurred in 28.6% of patients who underwent THA by fasciotomy performed 2 cm away from the intermuscular space [16]. This suggests that the conventional approach also poses a risk of LFCN injury for non-fan variation LFCN.

In the anterolateral approach (ALA), the incision is made further away from the fascia in order to reach the hip joint from between the tensor fasciae latae and gluteus medius. As with DAA, ALA is also an inter-muscular approach; thus, it enables preservation of the soft tissue and is associated with a relatively low risk of dislocation and rapid recovery of muscular strength after the procedure [17–21]. However, as both the tensor fasciae latae and gluteus medius are supplied by a motor nerve called the superior gluteal nerve, damage to the superior gluteal nerve due to ALA may reduce muscular strength [22, 23]. On the other hand, unlike DAA, LFCN injury is rarely reported after ALA [23].

Based on these findings, we hypothesized that the incidence of LFCN injury due to DAA-THA may be reduced by making the incision further away from where it is typically made in conventional fasciotomy. In this prospective study, we investigated how the position of fasciotomy in DAA-THA affects the risk of LFCN injury.

## Methods

### Study setting

This is a dual-center, double-blind, prospective randomized controlled two-arm trial with parallel group design in a 1:1 allocation ratio. The study is conducted in the Juntendo University Hospital and the Juntendo Tokyo Koto Geriatric Medical Center in Japan.

### Ethics and informed consent

The study was approved by the Research Ethics Board of Juntendo University Hospital in January 2019 and was subsequently registered in the University Hospital Medical Information Network (UMIN) clinical trials registry on February 20, 2019 (ID: UMIN000035945). The study team will explain about the study in writing and verbally, and voluntary written consent will be obtained from the patients. Patients will be informed immediately if any new information that may affect consent is obtained or if any changes to the study protocol that may affect consent will be implemented and will have the opportunity to decide whether they wish to continue participating in the study. We will also revise the consent form, and upon approval from the hospital’s research ethics board, we will provide the revised form to the study subjects to receive consent.

### Eligibility criteria

Patients aged 20 to 90 years who will undergo primary THA using the DAA, have a non-fan variation LFCN confirmed by ultrasonography before THA, and will have provided written informed consent for participation will be eligible. Patients with hip trauma or infection, body mass index ≥ 35, a history of hip surgery, inability to follow physician instructions, and those deemed unsuitable for inclusion by the principal investigator, such as neurological disorder, illiterate patients, or patients with severe medical conditions, will not be enrolled.

### Sample size

A sample size of 144 subjects is planned. According to our previous study, the overall incidence of LFCN injury incidence after DAA for THA is 42%, and the incidence of non-fan variation is 28.6% [16]. Thus, we hypothesize the lateral DAA approach will reduce the rate of LFCN injury to 10%. Using an alpha error of 5% and a power of 80% in two-tailed analysis, 124 subjects need to be recruited. These calculations were performed using SAS software version 9.4 (SAS Institute, Cary, NC, USA). Considering the dropout, we will enroll a minimum of 72 patients in each group.

### Recruitment and allocation

Patients who meet the eligibility criteria and have a non-fan variation LFCN confirmed by ultrasonography will be enrolled after written informed consent is obtained. Participants will be enrolled by the surgeon and assigned to interventions by the ultrasound inspector. Ultrasonography will be performed in the operating room before surgery to classify the LFCN as fan variation or non-fan variation. The surgeon will confirm the adherence of ultrasound protocol. After ultrasonography, the inspector will direct the surgeon to perform a lateral or conventional DAA according to the allocation table. The allocation table will be created in advance by a statistician and use a permuted block randomization schedule with a fixed block size of 4. The table will be stored by the ultrasound inspectors and concealed until the patient is assigned. Surgery will be performed as directed by the inspector. The trial flow chart is shown in Fig. 1.

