### Blinding

The statistician, participants, follow-up observer, and data analyst will be blinded to the surgical approach used in each participant. However, surgeons cannot be blinded because of their participation in the procedure.

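### The ultrasound inspectors who make the eligibility scan also keep the allocation table, so concealment is asserted but not secured

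*Protocol article*

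**What the plan says.** Under Eligibility criteria, patients must "have a non-fan variation LFCN confirmed by ultrasonography before THA". Recruitment and allocation says when and where this is settled: "Ultrasonography will be performed in the operating room before surgery to classify the LFCN as fan variation or non-fan variation". The same section gives the roles: "Participants will be enrolled by the surgeon and assigned to interventions by the ultrasound inspector". It continues: "After ultrasonography, the inspector will direct the surgeon to perform a lateral or conventional DAA according to the allocation table". On custody: "The table will be stored by the ultrasound inspectors and concealed until the patient is assigned". The surgeon's part in the scan is to confirm that the ultrasound protocol was followed.

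The schedule is to "use a permuted block randomization schedule with a fixed block size of 4". The abstract says that patients receive the two approaches "in the order specified in the allocation table created in advance by our clinical trial center", so a body outside the operating room already produces the list.

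The Blinding section names the statistician, participants, follow-up observer and data analyst as blinded. It then says: "However, surgeons cannot be blinded because of their participation in the procedure". The ultrasound inspector is not on the blinded list.

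**The concern.** Allocation concealment protects the comparison only if whoever decides that a patient enters cannot know the next arm. Here the last entry decision is the fan/non-fan reading, and the role that makes the scan keeps the list. The article names no independent keeper and no step that fixes the reading before the table is consulted.

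The reading leaves room for judgement. Under Ultrasonography of LFCN, non-fan means one main nerve with several smaller branches. Fan includes three or more branches of similar size, or at least two nerves arising from one main nerve. An intermediate pattern could be read either way, and the Discussion concedes as a limitation that no study exists on detecting the two types.

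The reading also bears directly on the primary outcome, because injury is far commoner in fan-type nerves. If doubtful nerves were called fan more often before one arm than before the other, the arms would differ in baseline risk. Blinding of patients and follow-up observers acts after entry and cannot restore the balance.

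**Working it through.** The article gives no figure for predictability or selection bias, so there is none to reproduce. Three checks were made.

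**1. Who can know what, and when.**

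| Step | Done by | Knowledge of the next arm |
|---|---|---|
| Enrolment | Surgeon | Unblinded; knows own past cases |
| Scan deciding eligibility | Ultrasound inspector | Keeps the table |
| Check that the scan followed protocol | Surgeon | As above |
| Assignment | Ultrasound inspector | Reads the table |

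No step between scan and assignment belongs to someone outside these two roles. An inspector who consulted the table early would know the next arm whatever the block size.

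**2. What fixed blocks of 4 add for the surgeon.** There are 6 equally likely 2:2 sequences. For someone who sees every earlier assignment and knows the block size and boundaries:

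- Known with certainty, positions 1 to 4: 0, 0, 1/3, 1. Mean = 1.333/4 = 33.3%.
- Guessed correctly, positions 1 to 4: 1/2, 2/3, 2/3, 1. Mean = 2.833/4 = 70.8%, against 50% by chance.

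These are upper bounds. Surgical procedures of THA lists five surgeons. Suppose (assumption) that they share one list, exchange no information, and each sees an earlier assignment with probability q = 0.2:

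- Certain: q²/3 = 0.04/3 = 1.3%.
- Guessed, positions 1 to 4: 0.500, 0.533, 0.560, 0.584. Mean = 54.4%.

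At q = 0.5 the figures are 8.3% and 59.9%; at q = 0.8 they are 21.3% and 65.7%. With full sight, larger fixed blocks help only a little: 68.3% guessable with blocks of 6 and 66.6% with blocks of 8.

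**3. What steering could do to the test.** Inputs:

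- No true effect of the approach.
- 65 per arm (half of the 130 in the second Sample size section, read as a total).
- Injury 20% in clear non-fan nerves (assumption).
- Injury 90% in borderline nerves (assumption, borrowed from the 9 of 10 in fan type).
- B = share of candidates with a borderline nerve (assumption).
- f = share of those called fan whenever the next slot is lateral (assumption).

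Formulas:

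- Conventional rate = 0.20 + 0.70 × B
- Borderline share left in the lateral arm: s = B(1 − f)/(1 − Bf)
- Lateral rate = 0.20 + 0.70 × s

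Example, B = 0.10 and f = 0.25: s = 0.075/0.975 = 0.0769, giving 27.0% against 25.4%. The last column is the exact probability that the two-sided 5% chi-square test rejects.

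| B | f | Conventional | Lateral | Type I error |
|---|---|---|---|---|
| 10% | 0 | 27.0% | 27.0% | 5.2% |
| 10% | 25% | 27.0% | 25.4% | 5.7% |
| 10% | 50% | 27.0% | 23.7% | 7.4% |
| 10% | 100% | 27.0% | 20.0% | 15.7% |
| 20% | 25% | 34.0% | 31.1% | 6.7% |
| 20% | 50% | 34.0% | 27.8% | 12.3% |
| 20% | 100% | 34.0% | 20.0% | 44.5% |

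A second version uses the article's own rates (28.6% and 90%) and 72 per arm. If 5% or 10% of one arm (assumption) were fan-type patients passed as non-fan, that arm's rate would rise by 0.05 × 61.4 = 3.1 or 0.10 × 61.4 = 6.1 points. Type I error would be about 7% or 12%. The two Sample size sections hypothesise reductions of 28.6 − 10 = 18.6 and 28.6 − 15 = 13.6 points.

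**The case against.** The strongest reply is that the article does state concealment until assignment. Sealing or envelope procedures may stand in a full protocol, and the flow chart is not visible here. This stands as far as it goes. A reader might infer that allocation is open to those selecting patients or that inspectors look ahead, and the text supports neither. What remains is that custody is stated, not omitted, and lies with the eligibility assessor.

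A reader might also infer that the surgeon sees every past allocation and so guesses 71% correctly. With five surgeons at two hospitals, this is not shown. Consent can also precede surgery by weeks (a 1-month pre-observation period), which weakens any link between the surgeon's initial selection and the next slot. Nor can one conclude that a single table serves both hospitals: the article does not say whether there is one list or one per centre.

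Finally, the 16% and 45% figures need every borderline nerve to be steered in the same direction, and they give borderline nerves a rate observed in nerves classified as fan. The article reports no borderline share. They are worst cases; lighter steering leaves the error between 6% and 12%.

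**Conclusion.** The point holds as a weakness in the stated arrangement. The inspectors scan for eligibility, keep the table and issue the assignment, and the only stated check is by an unblinded surgeon who enrols. That the inspector alone makes the classification is implied by the roles, not stated word for word.

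Fixed blocks of 4 are a secondary weakness: at most 33% of assignments certain and 71% guessable, and about 54% guessable for a surgeon who sees one earlier assignment in five.

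The bias cannot be estimated from the document. Under the stated assumptions type I error runs from about 6% (10% borderline, a quarter steered) to 16% (10%, all steered) or 45% (20%, all steered). The direction of risk is clear and its size is not. The evidence shows a vulnerability, not a breach. It matters because a positive result could not be firmly attributed to the fasciotomy site.

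**What to change.** For patients still to be enrolled:

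- Keep the table at the clinical trial center that creates it. Release one allocation at a time, by central release or sequentially numbered opaque sealed envelopes prepared there.
- Release it only after the fan/non-fan classification has been recorded irrevocably and time-stamped.
- Use varying block sizes that are not disclosed to the sites, and state whether lists are separate by centre. Custody is the main remedy; block size alone changes little.
- Log and report every patient scanned and classified as fan.

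For patients already enrolled, describe the custody arrangement in the report and list it as a limitation. Recruitment began in June 2019, the article appeared in July 2022, and completion is scheduled for March 2023, so the change cannot repair earlier allocations.

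The cost is an amendment and a short delay in the operating room while the allocation is released.

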**Fig. 1 Fig1:**
[figure not shown]
Flow chart of the trial protocol

### Blinding

The statistician, participants, follow-up observer, and data analyst will be blinded to the surgical approach used in each participant. However, surgeons cannot be blinded because of their participation in the procedure.

### Study timeline and data collection

After providing consent, study subjects will participate in the study for a total of 4 months, consisting of a 1-month pre-observation period and a 3-month post-observation period. The timeline for the assessment and data collection regarding primary and secondary outcomes is shown in Fig. 2.

**Fig. 2 Fig2:**
[figure not shown]
The schedule of enrolment, intervention, and assessments. WOMAC, Western Ontario and McMaster Universities Osteoarthritis Index; JHEQ, Japanese Orthopaedic Association Hip-disease Evaluation Questionnaire; FJS-12, Forgotten-Joint Score-12

### Ultrasonography of LFCN

Ultrasonography will be performed in the supine position using LOGIQ e Expert (GE health-care, Japan) with a 12-MHz linear array transducer according to the protocol developed by Zhu et al. [24]. First, the transducer will be placed perpendicular to the body axis and 1–2 cm away from the outer edge of the inguinal ligament. At this location, images of the sartorius and tensor fasciae latae muscles will be collected, and the LFCN between the muscles will be identified. While keeping the LFCN in the imaging field, the probe will be moved distally between the sartorius and tensor fasciae latae muscles (Fig. 3A). The LFCN is a structure in between the sartorius and tensor fasciae latae muscles that is characterized by a low signal intensity (nerve bundle) area surrounded by an oval or spindle-shaped high signal intensity (perineurium) area [24]. Fan variation and non-fan variation LFCN will be defined based on the pathological findings reported by Rudin et al. [15]. Specifically, non-fan variation LFCN is defined as a structure with one main nerve surrounded by multiple smaller branches (Fig. 3B) and fan variation LFCN as a structure with three or more branches of similar size or two or more nerves branching out from one main nerve (Fig. 3C) [15].

**Fig. 3 Fig3:**
[figure not shown]
**A** Schematic diagram showing the initial location of the probe. The probe is moved from the proximal to distal hip joint along the region between the sartorius and tensor fasciae latae muscles (arrow). ASIS, anterior superior iliac spine; TFL, tensor fasciae latae; S, sartorius. **B** Transverse ultrasound image of the non-fan variation within the intermuscular space between the sartorius and the tensor fasciae latae (yellow arrow: main branch, White arrow: thin branch). TFL, tensor fasciae latae; S, sartorius. **C** Transverse ultrasound image of the fan variation within the intermuscular space between the sartorius and the tensor fasciae latae (arrows: several nerve branches). TFL, tensor fasciae latae; S, sartorius

### Surgical procedures of THA

In all cases, THA will be performed under general anesthesia by one of five experienced (> 50 cases) hip surgeons [9, 25]. The surgery will be performed with at least two research team members, including the surgeon and research coordinators, to ensure that there is adherence to the protocol. Study subjects will be placed in the supine position, and the procedures will be performed with traction beds and intraoperative fluoroscopy [26]. The skin incision will be made 2 cm distally from the superior anterior iliac spine and in parallel with the line that connects the superior anterior iliac spine with the head of the fibula. The total length of the incision will be 10 cm. The same techniques will be used to set up the surgical field and place the implants for both groups. The same implant will be used for both groups.

### Interventions

The conventional approach involves incision of the skin, followed by incision of the fascia just below the site of skin incision. On the other hand, the lateral approach proceeds outside from the site of skin incision and involves incision of the fascia at a site 2 cm lateral from the conventional site of incision. Incision of the fascia will be performed to the extent that both approaches can be viewed in the surgical field (Fig. 4).

**Fig. 4 Fig4:**
[figure not shown]
Schematic diagram showing the line of fascia incision in conventional and lateral approach (red solid line: the site of fascia incision in lateral approach, red dotted line: the site of fascia incision in conventional approach). TFL, tensor fasciae latae; S, sartorius; LFCN, lateral femoral cutaneous nerve

### Standard of care

All patients will receive the standard routine post-operative management protocol of a wound review and a further review using X-ray at postoperative and 3 months follow-up. Postoperative rehabilitation and physiotherapy will be standardized according to our institutional protocol and initiated for all patients at day 1 post-operatively.

### Withdrawal criteria

Study subjects will be withdrawn from the study if the principal investigator and the study team decide that it is impossible to continue the study activities under the study’s criteria. If this applies, the subject will be given an explanation for their withdrawal. The withdrawal criteria will be:If withdrawal from the study is requested or if consent is withdrawn by a study subject,If the study is terminated, orIf the principal investigator decides that the study should be terminated for reasons other than those listed above.

Withdrawal patients will continue to receive routine as required. Participants who withdrawal or are withdrawn from the study interventions will be followed up as per intention to treat, unless consent has been fully withdrawn.

